### Sample size and recruitment

The required sample is 60 young people, 30 per study arm. This is large enough to test the feasibility of the research procedures and to establish a mean and SD on each outcome measure.^42^ Five young people are to be randomised into the study each month. Recruitment rates and the final target will be used to inform the decision to proceed to a definitive trial.

Attrition will be minimised by having robust trial procedures to prevent data loss. Procedures have been developed with our patient and public involvement (PPI) groups and tested for maintaining contact with participants. Recognising that this population can be difficult to follow-up, follow-up data collection points will occur within broad time windows. Having very broad time windows allows for as many follow-ups to be completed within the CYPSE, but also ensuring that no young people are excluded from the study if they miss a follow-up.

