**Methods and analysis:**

A single-centre parallel group feasibility randomised controlled trial will be conducted. Sixty young people within the CYPSE identified as displaying possible symptoms of ADHD will be randomised to the intervention arm (n=30; QbTest plus usual care) or control arm (n=30; usual care). Primary analyses will be descriptive and a process evaluation will be conducted to assess the contexts involved in implementing the intervention. Interviews will be conducted to explore acceptability and thematic analysis will be used to analyse the data.

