### Trial design

A parallel two-group randomised controlled trial with 1:1 individual participant allocation to QbTest plus usual care (n=30; intervention group) or usual care alone (n=30; control group) with a parallel process evaluation. Recruitment started in March 2019 and is due to last 12 months.

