### Data analysis and management

Data analysis will be mainly descriptive.^44^ All measures will be summarised by group across follow-up time with mean and SD for normally distributed data, median for skewed variables and frequency (percentage) for categorical data. All statistical analysis will be conducted using Stata V.15. No interim analysis is planned.

Interviews will be conducted and recorded by the researcher using an encrypted Dictaphone. All qualitative data will be analysed using thematic analysis^45^ with the aid of NVivo. Data will be coded inductively into themes, creating a detailed coding scheme, allowing for the investigation of emergent patterns between individual codes and boarder emergent themes.

Data will be double entered and stored on an encrypted and password-protected database at the University of Manchester. Double-entered data will be compared for discrepancies and discrepant data will be verified using the original paper data sheets (between [name] and CL).

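### The sample size is justified by a mean and SD for every outcome, but the analysis rule gives skewed outcomes only a median, and the 30 per arm are randomised rather than followed up

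*Protocol article*

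**What the plan says.** The protocol article, under Sample size and recruitment, states: "The required sample is 60 young people, 30 per study arm". The reason follows directly: "This is large enough to test the feasibility of the research procedures and to establish a mean and SD on each outcome measure". The claim covers every outcome measure and carries no precision target.

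Under Data analysis and management, the choice of summary depends on the shape of the data: "mean and SD for normally distributed data, median for skewed variables", with frequencies and percentages for categorical data. No measure of spread accompanies the median.

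The 60 are people randomised. The abstract says "Sixty young people within the CYPSE identified as displaying possible symptoms of ADHD will be randomised", and the sample size section says "Five young people are to be randomised into the study each month". No retention figure is assumed, although the same section writes: "Recognising that this population can be difficult to follow-up". It responds with contact procedures and broad follow-up windows.

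The Secondary outcomes section lists questionnaire and rating scores at baseline, 3 and 6 months. It also lists the number and length of appointments up to diagnosis, days to diagnosis, service contacts, and behavioural incidents and adjudications.

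**The concern.** A feasibility trial that is sized to yield a mean and SD for each outcome should report them for each outcome. Here the reporting rule removes both whenever a variable is judged skewed. The outcomes most exposed are durations and counts. The Introduction names time to diagnosis as the primary outcome of previous QbTest trials and asks whether outcomes such as aggressive incidents matter more in this population. Those are the outcomes for which planning figures may be wanted, and a median with no spread gives little to plan from.

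The second element is smaller. A reader may take the sample size statement to mean that 30 values per arm will stand behind each mean and SD. At 3 and 6 months that would require complete follow-up, which the protocol itself does not expect to be easy.

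**Working it through.** **1. The plan's own figure.** There is no power formula to reproduce. The recruitment statements are "Five young people are to be randomised into the study each month" and "Recruitment started in March 2019 and is due to last 12 months". So 5 × 12 = 60, and with 1:1 allocation 60 / 2 = 30 per arm. This reproduces the stated size and confirms that it counts people randomised, with no addition for loss.

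**2. The two statements side by side.**

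| Type of outcome | Sample size section promises | Analysis section reports |
|---|---|---|
| Continuous, judged normal | Mean and SD | Mean and SD |
| Continuous or count, judged skewed | Mean and SD | Median only |
| Categorical | Not applicable | Frequency and percentage |

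The second row is the conflict. The article does not say which outcomes are skewed. Placing days to diagnosis, appointment numbers and minutes, service contacts, incidents and adjudications in that row is a judgement from their type: they are non-negative durations and counts, which often have a long right tail.

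**3. What the randomised number means for an SD at follow-up.** For a roughly normal outcome, the 95% CI of an SD, as a multiple of the estimate, runs from √(df / χ²(0.975, df)) to √(df / χ²(0.025, df)). Here df = n − 1 for one arm and n − 2 for two arms pooled. The article gives no attrition rate, so 30% loss is assumed for illustration: 30 × 0.7 = 21 per arm, 42 in total.

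- 30 in one arm, df 29: √(29/45.72) = 0.80 and √(29/16.05) = 1.34.
- 21 in one arm, df 20: √(20/34.17) = 0.77 and √(20/9.59) = 1.44.
- 42 pooled, df 40: √(40/59.34) = 0.82 and √(40/24.43) = 1.28.

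Over a wider assumed range, the one-arm interval is 0.78 to 1.40 at 20% loss (24 per arm), 0.75 to 1.50 at 40% (18) and 0.73 to 1.58 at 50% (15).

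**4. Limits of step 3.** The interval assumes normal data, so it describes the questionnaire scores at best and should not be applied to the skewed outcomes in step 2. Baseline summaries are unaffected by loss to follow-up.

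**The case against.** The best defence is that little is lost for good. The raw data are collected, so an SD can be calculated at any time, and a fuller analysis plan may well add an IQR. It can also be said that a plain SD is not the natural planning figure for these outcomes. Time to diagnosis is unobserved for anyone undiagnosed at the end of follow-up, and the Introduction itself quotes an earlier trial's result as the proportions with a decision at 6 months (76% and 50%). Incident counts would usually be planned on a rate and its dispersion. This keeps the point modest. It does not remove it, because the article states a purpose and then a rule that defeats it, and an IQR added elsewhere would still not supply a mean and SD on each measure.

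On attrition the defence is stronger. Attrition is a primary outcome, so the trial is partly meant to learn that figure. No number of completers is promised. For retention, the consented or randomised group is the right denominator. An SD can still be calculated at every loss level considered above.

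A reader might infer more than the document supports:

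- **That 60 is too few.** Without a precision target there is nothing for 60 to fall short of.
- **That a definitive trial could be undersized about twofold.** Squaring 1.44 gives 2.1, but that uses one arm of 21 under an assumed loss. A full arm of 30 already gives 1.34² = 1.8, and pooling 42 gives 1.28² = 1.6. The article also does not say that these SDs would be carried forward unadjusted.
- **That confidence intervals have been wrongly left out.** That is detail an analysis plan commonly holds.

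**Conclusion.** The conflict between the sample size rationale and the reporting rule stands on the text alone. One section promises a mean and SD for each outcome, and the other withholds both from any skewed outcome and names no spread. How many outcomes are affected depends on the judgement that durations and counts here will be skewed. If that is right, it includes the two kinds of outcome that the Introduction discusses as candidates for a later trial.

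The attrition element is a clarification. Under an assumed 30% loss, the upper limit for a one-arm SD of a roughly normal outcome moves from 1.34 to 1.44 times the estimate. Most of the imprecision is present at 30 per arm already. No feasibility conclusion is affected.

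**What to change.** In Data analysis and management, report n, mean and SD together with median and IQR for every continuous or count outcome, whatever its shape. The alternative is to limit the claim in Sample size and recruitment to the outcomes for which an SD will be reported. The first option is better because it keeps the stated purpose.

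In Sample size and recruitment, add that 30 per arm is the number randomised and that follow-up means and SDs will rest on fewer. The precision for roughly normal outcomes can be given alongside: 0.80 to 1.34 at 30 per arm, 0.77 to 1.44 at 21, and 0.82 to 1.28 pooled over 42, with the 30% loss labelled as an assumption.

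The cost is two sentences and a few table columns. No extra participants or data collection are needed.

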### Randomisation and blinding

Randomisation will be achieved by means of concealed random allocation conducted using an online pseudorandom list hosted by Sealedenvelope.com with random permuted blocks of varying sizes. Randomisation will be undertaken by the researcher, who will inform healthcare staff of trial arm allocation.

Given the nature of the intervention, it is not possible to blind participants or those involved in delivering the intervention. It is also not possible to blind the field researcher due to the researcher and staff delivering the intervention working within the confines of a secure environment. It is also not possible to use a second researcher to collect follow-up data (who does not know trial arm allocation) as this is logistically very challenging and ultimately conflicts with the idea of building a strong researcher–participant relationship to enhance follow-up rates. Therefore, to minimise any potential bias, protocolising the collection of outcome measures which will be overseen by the onsite principal investigator and trial manager (CL). None of the outcome measures completed by the young person with the researcher present are particularly susceptible to bias as they are standardised, self-complete questionnaires. The researcher may need to support the young person in completing questionnaires due to literacy levels and protocolising collection ensures that support is consistent and unbiased. The study statistician ([name]) will be blind to arm allocation.

#### Data collection

See table 1 for a summary of the study schedule of data collection.

**Table 1 T1:** Summary of study schedule

Timepoint		Screening	Baseline	Allocation	Follow-up	
		t0	t1		+3 mth t2	+6 mth t3
Enrolment:						
Eligibility screen		X				
Informed consent		X				
*Parental consent (* *<* *16)*		X				
Allocation				X		
Interventions:						
*Intervention group:*	*QbTest*					
	Usual care					
*Control group:*	*Usual care*					
Assessments:						
*Demographics*			X		X	
*SDQ*			X		X	
*B-BAARS*			X		X	
*CHU-9D*			X		X	
*SNAP-IV*			X		X	
*C-GAS*			X		X	
*ADHD diagnosis* *and* *clinical confidence*					X	
*Health records*			X		X	
*Prison records*			X		X	
*Modified CSRI*			X		X	
*Contact sheet*			X		X	
Safety monitoring:						
Adverse event reporting						

ADHD, attention deficit hyperactivity disorder; B-BAARS, Brief Barkley ADHD Rating Scale; C-GAS, Children's Global Assessment Scale; CHU-9D, Child Health Utility Instrument; CSRI, Client Service Receipt Inventory; SDQ, Strengths and Difficulties Questionnaire; SNAP-IV, Swanson, Nolan and Pelham Questionnaire.

#### Baseline data collection (t1)

The researcher will deliver the baseline data collection interview using a narrative conversational format. Demographics and questions from other measures are incorporated into a specially constructed flexible paper case report form which avoids duplication of subject matter in order to reduce disengagement or irritability.

#### Follow-up (t2–t3)

If the young person is to be released during the study, the researcher will meet with them usually within the week prior to release. During this meeting, the researcher will confirm the contact information provided at baseline and make any amendments to the information (eg, change of phone number). Once discharged, the researcher will contact the participant again in the community, to maintain engagement, confirm contact details and arrange the follow-up in the community.

The 3-month follow-up can take place between 61 and 151 days post randomisation, although the researcher will endeavour to complete data collection as close to the 3-month (90-day) point. The 6-month follow-up can take place between 152 and 244 days postrandomisation, although the researcher will endeavour to complete data collection close to the 6-month point (182 days).

The follow-up may take place in prison or in the community, depending on if the young person has been discharged. In the community, the researcher will arrange to meet the young person at a convenient location. Where possible, interviews will be conducted in the premises of services that the young person is engaged with in order to minimise risk to the researcher. Where this is not possible, the researcher will arrange to conduct the interviews in a suitable location in the community and adhere to the Local Lone Working Policy.

### Process evaluation

QbTest in itself may not be defined as a complex intervention requiring a process evaluation to understand the mechanisms of impact, for example, how QbTest produces change; however, delivering an intervention within a criminal justice setting is complex. Understanding the effects of the context as barriers or facilitators is critical for interpreting the findings and generalising beyond it to a full trial. The process evaluation will follow the MRC guidelines^43^ and will be conducted in parallel to the trial and will assess:

the acceptability of randomisation (interviews);the acceptability of outcome measures (completeness of each measure and interviews);the numbers of young people agreeing to sit the QbTest and the number who complete QbTest;feedback from young people receiving the QbTest and health professionals using a questionnaire;the acceptability of the QbTest via interviews with young people; andhealth professionals and other CYPSE staff to obtain perspectives on facilitators and barriers to using the QbTest.

### Data collection

QbTest completion rates: a record will be taken of the numbers of participants who agree to sit and also complete the QbTest.

QbTest opinion questionnaire: all young people who receive QbTest will be asked to complete the QbTest opinion questionnaire at 3 months. The questionnaire contains 11 questions, for example, ‘the QbTest results were difficult to understand’ and the young person is asked to rate each item on a 5-point scale. At month 15, clinicians involved in the QbTest will be asked to complete the clinician version, which contains 13 questions rated on a 5-point scale and two free-text response questions.^29^

Interviews with young people: randomisation: a subsample of young people in both trial arms will be interviewed using a semistructured interview schedule to further explore acceptability of the randomisation process. Young person’s age and time of randomisation (beginning or end of study) will be used to purposively select the sample. Outcomes: a subsample of young people in both trial arms will be interviewed using a semistructured interview schedule to further explore acceptability of completion of the outcome measures. Young person’s age and time of randomisation (beginning or end of study) will be used to purposively select the sample. QbTest: a subsample of young people who receive QbTest will be interviewed using a semistructured interview schedule to further explore acceptability of the QbTest and its administration as well as study processes and procedures. Scores/responses in the QbTest opinion questionnaire, young person’s age and whether or not the QbTest was completed will be used to purposively select the sample. Up to 20 young people will be interviewed.

Interviews with healthcare professionals and CYPSE staff: healthcare professionals and CYPSE staff will be invited to participate in qualitative interviews to further explore acceptability and feasibility of administering and implementing the QbTest within usual assessment practices and procedures, including the barriers to its use and reasons for non-completion. Scores/responses in the QbTest Opinion Questionnaire will be used to purposively select healthcare professionals. Up to 10 professionals will be interviewed.

### Data analysis and management

Data analysis will be mainly descriptive.^44^ All measures will be summarised by group across follow-up time with mean and SD for normally distributed data, median for skewed variables and frequency (percentage) for categorical data. All statistical analysis will be conducted using Stata V.15. No interim analysis is planned.

Interviews will be conducted and recorded by the researcher using an encrypted Dictaphone. All qualitative data will be analysed using thematic analysis^45^ with the aid of NVivo. Data will be coded inductively into themes, creating a detailed coding scheme, allowing for the investigation of emergent patterns between individual codes and boarder emergent themes.

Data will be double entered and stored on an encrypted and password-protected database at the University of Manchester. Double-entered data will be compared for discrepancies and discrepant data will be verified using the original paper data sheets (between [name] and CL).

### Monitoring

#### Adverse events

Serious adverse events (SAEs) will be recorded by the research team and reported to the chief investigator and Trial Steering Committee (TSC). Any SAEs deemed to have a causal relationship to trial participation will be reported to the sponsor within 24 hours of the chief investigator being informed.

#### Trial management and oversight

The TSC will oversee the conduct and safety of the trial and includes the role of the data monitoring. The committee includes an independent chair, independent members, a patient and public representative and the chief investigator. Representatives from both the sponsor and funding organisations will be invited to study-related elements of the TSC meetings as observers. The TSC will meet quarterly.

#### Audit

The trial coordinator or a nominated designee of the sponsor shall carry out monitoring of trial data as an ongoing activity. Trial data and evidence of monitoring and audits will be made available for inspection by the research ethics committee as required.

## Ethics and dissemination

Health research authority approvals have been granted. Only the research team will have access to the study data, which will be stored in secure locked files or password-protected databases. Data will be available for inspection by the ethics committee on request. Changes to the protocol will be communicated to the ethics committee and trial registries by the trial manager (CL).

### Consent process

Obtaining informed consent or assent will be in accordance with ethical guidance and good clinical practice. The researcher will be trained to assess for capacity to consent in young people. This will include assessing if the young person has the ability to understand the information relevant to the decision, retain the information, use or weigh the information as part of the process for decision-making and communicate the decision to the researcher.

The researcher will explain what participation in the study involves and how much time will be involved. They will also explain that participation is voluntary, that they can withdraw at any time and at any point and that their decision to participate, or not, will have no adverse effect on the care that they receive or their other legal rights. The researcher will also discuss the arrangements in place to ensure confidentiality (and limits of this) and data protection. Throughout this process, the potential participant will be given an opportunity to ask questions. Potential participants will be made aware of circumstances in which confidentiality would be broken (if they or someone else identified may be at potential risk of harm; for example, self-harm, breaches of security and violence, including acts of terrorism/radicalisation).

Having had the opportunity to discuss their involvement in the study and ask questions about it, potential participants will be asked if they would like time (minimum 24 hours) to consider taking part or if they would like to sign the consent form (online supplementary file 1—consent form) if they are willing to take part.

10.1136/bmjopen-2019-035519.supp1Supplementary data

### Patient and Public Involvement

PPI significantly informs and impacts on this project. NB (coapplicant and coauthor) is the project PPI representative and is directly involved in the project providing her lived experience expertise throughout the project ensuring that the perspective of young people with ADHD and their parents are considered throughout. The project has PPI representatives from the community and also within the CYPSE and both groups have helped develop the information leaflets for the study and also helped develop and refine research procedures, for example, how best to explain what participation in the study involves and how best to achieve community follow-ups. The CYPSE PPI group meet with the researcher ([name]) on a regular basis to feed into the project. The PPI groups will be involved in the analysis, reporting and dissemination of the research.

### Dissemination

The findings from the trial will be used to inform the design, feasibility and acceptability of a future definitive trial. The findings will be published in peer-reviewed journals, presented at relevant conferences and disseminated to the public via summaries cocreated with our PPI group.

## Discussion

Secure settings are complex environments in which to conduct trials^46^ and there is a dearth of trials within the CYPSE. In the context of this challenging environment, a decision will be taken as to whether feasibility and acceptability are adequate for a full multicentre randomised controlled trial.

Current service provision for ADHD in the CYPSE is ad hoc and uncoordinated. There is growing evidence within community settings^30 32–34^ that QbTest has the potential to significantly improve the current assessment pathway having a direct impact on young people’s health, service delivery and criminal justice outcome.
